#### Measurement procedures

In each practice measurements are done at baseline and at follow-up (Figure 1). At baseline, medical records of 40 patients with established CVD are audited as part of the clinical performance measurements in the practice accreditation program. Data on performance indicators of CVRM as included in the practice accreditation program will be used for the analysis. At follow up, the following measurement methods will be used: medical record audit based on the same indicators of CVRM as in the baseline measurement, patient questionnaires, and a semi-structured interview for a contact person in each practice. Data will be collected consistently as this is done by two persons with similar training.

**Figure 1 F1:**
[figure not shown]
Flow Diagram.

#### Measures of effectiveness

The effect evaluation aims to determine the effectiveness of the program on primary performance indicators for CVRM and to determine the potential impact of the program on other indicators for CVRM, self-reported goal attainment in the intervention group, and unintended consequences.

Primary outcomes have been selected from the 20 quality indicators for established CVD [21], which were developed by DCGP (Table 1), and are:

1. The percentage of patients in the practice with known established CVD who have systolic blood pressure below 140 mmHg.

2. The percentage of patients in the practice with known established CVD who have LDL cholesterol below 2.5 mmol/l.

3. The percentage of patients in the practice with known established CVD with a record that aspirin, an alternative anti-platelet therapy, or an anticoagulant has been prescribed.

**Table 1 T1:** Indicators for cardiovascular risk management

**Type of indicator**	
Process	Smoking status
Outcome	Patient is a smoker
Process	Stop smoking advice
Process	BMI measured
Outcome	BMI < 25 kg/m^2^
Process	Influenza vaccination
Process	Exercise control
Process	Systolic blood pressure measured
Outcome	Systolic blood pressure < 140 mmHg^1^
Process	LDL cholesterol measured
Outcome	LDL cholesterol <2.5 mmol/L^1^
Process	Advice physical activity
Process	Diet control
Process	Counseling about diet
Process	Registration of alcohol intake
Process	Patients with LDL cholesterol ≥2.5 mmol/L with statin prescription
Process	Waist circumference measured
Process	Prescription antiplatelet drugs^1^
Process	Fasting glucose measured
Process	Comprehensive risk assessment *

*Positive score when there is a record of: blood pressure, BMI, waist circumference, fasting glucose measurement, LDL cholesterol measurement, smoking behavior, alcohol intake, advice and control of diet and physical exercise in the past 12 months.

^1^Primary outcome.

Data concerning indicators are extracted from medical records and will be available at patient level so that linkage to other measures (resource use, patient characteristics) can be made at patient level.

Secondary outcomes consist of the 17 remaining indicators are used and include: measurement of systolic blood pressure, measurement of LDL-cholesterol, prescription of statin, smoking status, stop smoking advice, measurement of body mass index (BMI), BMI <25 kg/m^2^, measurement of waist circumference, fasting glucose measurement, influenza vaccination, registration of alcohol intake, control and advice for exercise and diet, and comprehensive risk assessment (Table 1). Furthermore, secondary outcomes are measured in interviews with the contact person of the practice and contain perceived goal attainment regarding the improvement plans, which is measured on a likert scale, and unintended consequences as result of participating in the practice accreditation program.

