#### Intervention group

The intervention starts with volunteering for the practice accreditation program. After enrolment for the study, practices will be contacted by telephone for further explanation of the study protocol and to schedule the data collection. After data is collected, practices are randomized. Practices allocated to the intervention group are instructed to focus their improvement plans on cardiovascular diseases in the first year of the program.

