#### Control group

The control group also starts with volunteering for the practice accreditation program and follows the same routine as described for the intervention group. Practices allocated to the control group are instructed to focus their improvement plans on other domains than cardiovascular disease and diabetes mellitus (they may target CVD later after the study period of one year). They are instructed to focus their improvement plans on other clinical areas than CVD or diabetes.

Both intervention and control group receive feedback on CVD indicators as part of the normal practice accreditation program. Practices in the intervention group are instructed to set targets related to process and outcomes of cardiovascular care (and not just focused on improvement of registration of cardiovascular disease in the medical record system). All practices will receive a minimum of four hours of support by outreach consultants for no cost, which is available in all regions. Also, the practices are provided with examples of improvement plans, which saves time and would make study participation more attractive.

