#### Sample size

In the practices in the practice accreditation program up to 2006 (n = 139), the following median values at practice level were found on indicators referring to patients with CVD: 53% for acceptable blood pressure levels; 36% for acceptable cholesterol levels; and 38% for use of anticoagulents (unpublished data at IQ healthcare, 2005 and 2006). These data suggest that the current scores on the primary outcomes are in the range of 35% to 55%, which imply that substantial improvement is possible in many practices. The proposed study has been powered to detect a difference of 10% (from 55% to 65%), not yet taking control for baseline values into account because of uncertainty regarding the correlation between baseline and follow-up measures.

We expected that the accreditation and improvement program will have an effect of 5% to 10% absolute change, which is the median value of effect sizes in a comprehensive review of 235 studies on quality improvement [14]. Other assumptions were a power = 0.80, alpha = 0.05, and ICC = 0.05. Given the sample of 30 patients per practice per indicator, we aimed to include 31 practices in each group. Allowing for dropout, we aim to include 35 practices in each group (n = 70 practices in total). This number is feasible, given the recruitment rate for the accreditation in 2006.

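### The statin indicator in Table 1 is scored only among patients with LDL of 2.5 mmol/L or higher, so if follow-up LDL defines that group, the between-arm comparison can stay flat or fall when treatment improves

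*Protocol article*

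**What the plan says.** Table 1 of the Protocol article lists, as a process indicator, "Patients with LDL cholesterol ≥2.5 mmol/L with statin prescription". The paragraph on secondary outcomes after the table names the same item without any LDL condition: "measurement of systolic blood pressure, measurement of LDL-cholesterol, prescription of statin, smoking status".

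Under Measures of effectiveness, the second primary outcome is "The percentage of patients in the practice with known established CVD who have LDL cholesterol below 2.5 mmol/l".

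On timing, the Intervention group section states "After data is collected, practices are randomized". Measurement procedures provides at follow-up for a "medical record audit based on the same indicators of CVRM as in the baseline measurement". On the aim of the intervention, the Control group section adds: "Practices in the intervention group are instructed to set targets related to process and outcomes of cardiovascular care".

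Statistical methods gives every primary outcome a logistic model in group and measurement moment, with random coefficients for practices, and applies the same approach to each secondary outcome. The article does not state whether the LDL value behind the statin indicator is the latest one or one taken before treatment.

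**The concern.** Among patients with a measured LDL, the statin indicator's denominator is everyone who fails the second primary outcome. The intervention is meant to move patients out of that group, and statin treatment is one way of doing so. If the follow-up LDL is used, three things follow.

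- A patient who is put on a statin and reaches target disappears from both numerator and denominator, so successful prescribing earns no credit.
- A patient already on a statin who reaches target also disappears, which lowers the indicator although nobody has stopped treatment.
- The two arms are compared on groups selected by a post-randomisation result, so randomisation no longer makes them comparable.

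At stake is the reading of one named secondary outcome. An intervention that improved both lipid control and statin prescribing could be reported as having no effect, or an adverse one, on statin prescribing. The difference in wording between table and text also leaves open which version will be tested.

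**Working it through.** **The plan's own calculation.** The article gives no figure for the statin indicator. Its sample size reproduces: 55% against 65%, two-sided alpha 0.05 (sidedness assumed) and power 0.80 need 376 patients per arm. The design effect is 1 + 29 × 0.05 = 2.45, and 376 × 2.45 / 30 = 30.7, so 31 practices per arm, as stated. Nothing below changes it.

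**Count illustration, per 100 patients, all with LDL measured.** From the protocol: 36% LDL control (Sample size section). Assumed: 26 of the 36 at target and 32 of the 64 not at target are on a statin.

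- Start: indicator 32/64 = 50%; statin use (26 + 32)/100 = 58%.
- Change: 8 untreated patients start a statin and 6 of them reach target; 10 patients already treated reach target.
- LDL control: 36 + 6 + 10 = 52%.
- Statin use: 58 + 8 = 66%.
- Indicator: (32 + 8 − 6 − 10)/(64 − 6 − 10) = 24/48 = 50%.

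The 16-point gain in LDL control exceeds the 5 to 10 points the protocol expects. Halving every change gives LDL control 44%, statin use 62% and an indicator of (32 + 4 − 3 − 5)/(64 − 3 − 5) = 28/56 = 50%, still flat.

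**General form.** Let s be the share on a statin, r the share of users with LDL below 2.5, and u the share of non-users with LDL below 2.5.

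- LDL control = s·r + (1 − s)·u
- Indicator = s(1 − r) / [s(1 − r) + (1 − s)(1 − u)]

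With assumed s = 60%, r = 50%, u = 15%, LDL control is 0.30 + 0.06 = 36%, matching the protocol. Holding u at 15%:

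| Scenario | s | r | LDL control | Indicator | Statin use, all patients |
|---|---|---|---|---|---|
| Baseline | 60% | 50% | 36.0% | 0.300/0.640 = 46.9% | 60% |
| Better control among users only | 60% | 66.7% | 46.0% | 0.200/0.540 = 37.0% | 60% |
| More starts and better control | 65% | 60% | 44.3% | 0.260/0.5575 = 46.6% | 65% |
| More of both | 70% | 70% | 53.5% | 0.210/0.465 = 45.2% | 70% |
| New starts only | 65% | 50% | 37.8% | 0.325/0.6225 = 52.2% | 65% |

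**Range.** Take s = 50%, 60%, 70% and u = 5%, 10%, 15%, with r solved so that baseline LDL control is 36%: nine combinations.

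- LDL control raised to 46% at unchanged statin use: the indicator falls in all nine, by 7 to 14 points. The extremes are 25.8% to 12.0% (s = 50%, u = 5%) and 60.2% to 52.8% (s = 70%, u = 15%).
- Statin use up 5 points and LDL control at 46%: change of −5.0 to +0.5 points.
- Statin use up 5 points with r unchanged: rise of 4 to 6 points.

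The all-patient measure follows statin use in every scenario. Per 30 patients, the conditional denominator also shrinks, from 30 × 0.64 = 19.2 to 30 × 0.54 = 16.2, when LDL control goes from 36% to 46%.

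**The case against.** Table 1 gives short labels for indicators taken from a cited set, and the full definition is not shown. A pre-treatment LDL would remove much of the problem, and the secondary-outcome text carries no LDL condition at all. This stands: the point is conditional on the follow-up LDL being used.

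A reader might infer that the bias is certain, or that the intervention necessarily shrinks the denominator. The documents do not support that. New starts with unchanged control among users raise the indicator. LDL measurement is itself an indicator, and more testing can bring previously unmeasured patients with high LDL into the group, so its size and mix can move either way.

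A reader might also extend the point to the blood pressure and LDL primaries, taking "Given the sample of 30 patients per practice per indicator" beside "At baseline, medical records of 40 patients with established CVD are audited" to mean that unmeasured patients are dropped, or arguing that better control could not be told from better recording. That does not hold:

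- The article does not explain the 30, which may be a planning allowance. The 40 describes the baseline audit only.
- Measures of effectiveness already sets the primary denominator as all known patients with established disease.
- Aims and objectives already describes the control outcomes as documented.
- The shares with blood pressure and LDL measured are separate secondary indicators under the same model.
- Intervention practices are told not to aim only at registration.

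Finally, this is one of 17 secondary indicators. That stands and limits the weight of the point.

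**Conclusion.** The point holds in conditional form. If follow-up LDL defines the group, the between-arm statin comparison conditions on a post-randomisation outcome that the intervention targets, and it can be biased. Under assumed inputs calibrated to the protocol's 36% LDL control, the indicator can stay at 50% while statin use rises by 8 points, and it falls by 7 to 14 points when LDL control rises by 10 points at constant statin use. Improvement through new starts alone moves it the right way.

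The sizes rest on assumed statin use, assumed control among users and non-users, and LDL being measured in everyone; the protocol gives none of these. The mismatch between Table 1 and the secondary-outcome text rests on no assumption. The primary outcomes and the sample size are not affected.

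**What to change.** Define the secondary outcome for the between-arm comparison as statin prescription among all audited patients with established cardiovascular disease. Keep the version restricted to LDL of 2.5 mmol/L or higher as descriptive, and state which LDL value defines it. Make Table 1 and the secondary-outcome paragraph agree.

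The cost is a line of wording and one more table column. Indicators are held at patient level (text after Table 1), and cardiovascular medication use is extracted from records at follow-up (Measures of costs), so the follow-up comparison needs no new data. There are two small drawbacks. Statin use at baseline may not have been recorded for patients with LDL below 2.5; this should be checked before the group-by-moment model is used for the new measure. The result will also differ from the accreditation program's standard indicator, which is a reason to keep reporting that one descriptively.

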#### Measures of costs

In follow-up measurements items of use of healthcare will be extracted from the medical records with a retrospective three-month observation period. These items include number of contacts in the practice (face to face, telephone, email), use of various types of cardiovascular medication, use of hospital care or other care providers for cardiovascular diagnosis or therapy. Additional information will be collected with patient questionnaires, particularly on other healthcare use (*e.g.*, home care) and productivity losses, using a one-month retrospective observation period. Also, at follow-up in both groups, time and other resources of practice teams spent on quality improvement in the total period of 18 months will be documented. Data-collection on performance indicators will be done in the follow-up measurement by medical record audit.

#### Other measures

1. Exposure to other quality improvement activities: Both study groups report on their exposure to relevant professional education and practice improvement activities (*e.g.*, training for practice nurses). This will be measured in semi-structured telephone interviews.

2. Potential confounders: At follow up, potential confounders will be measured. These include patient characteristics, particularly patient age, gender and multi-morbidity. Furthermore, data on practice characteristics will be collected. These include practice size, physician workload, volume of assistance in the practice, delegation of medical tasks to assistants, and involvement of practice nurses in chronic care. These practice characteristics have shown to be associated with better chronic disease management in Dutch primary care practices [22].

3. Patient reported outcomes: At follow up, patients receive questionnaires that include items on demographic characteristics, labor activities and healthcare use. Furthermore the EQ-5D (five items and VAS scale) will be added to measure health outcome [23]. To measure chronic care delivery, the Patient Assessment of Chronic Illness Care (PACIC) will be used [24]. Questionnaires for physical exercise (RAPA, nine items) [25], and the Treatment Self-Regulation Questionnaire (TSRQ) [26] to measure the motivation for being physically active will be included.

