#### Statistical methods

The study groups will be compared at baseline regarding known determinants of cardiovascular care and its improvement. These include patient factors [27,28] (*e.g.*, age, multi-morbidity, ethnicity at practice level) and practice characteristics [22,29] (*e.g.*, availability of nurses, delegation of medical tasks to assistance, practice size). Only factors emerging from previous research are considered to avoid overcorrection in the primary analysis. A logistic regression model will be constructed for each outcome to analyze these outcomes in relation to group (intervention, control) and measurement moment (baseline, follow-up). Identified differences between the groups at baseline will be included in this analysis. Random coefficients will be included to allow for the clustering of data within practices. Each of the secondary outcomes (clinical and organizational indicators) will also be analyzed in this way. Finally, if an internally consistent scale can be constructed (reflected by high reliability coefficients of the combined score), we will develop an aggregated measure of outcome, and use this in a similar random coefficients linear regression analysis.

To identify the effectiveness of this program on attainment of practice-defined goals and its perceived unintended consequences, the second key objective, a descriptive analysis will be performed aimed at determining what proportion of self-defined goals for improvement was achieved by the practices and straightforward listing of the GP views on unintended consequences of the practice accreditation program.

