#### Process evaluation

The process evaluation, the fourth key objective, aims to explore what factors and mechanisms are associated with change (or absence of change) of performance on CVRM indicators. Semi-structured telephone interviews will be held with primary care physician or the quality coordinator of the practice after data collection for follow-up measurement is concluded. Topics of this interview are: practice characteristics; feedback reports; composing improvement plans; and reasons to participate in and experiences with the practice accreditation program. We want to explore if specific elements of the practice accreditation program are the cause of change in CVRM. All interviews will be conducted by the same person and will be audio-recorded. Interviews will be transcribed verbatim. Two researchers will independently review the transcripts. Data analysis will be done according to the framework approach [31]. Topics in the interviews will be used as coding frame. Software package Atlas ti. will be applied to analyze qualitative data. The primary analysis of the interview data aims to identify determinants of (change of) practice as perceived by participants.

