## Discussion

The sample of participating primary care practices in this study is composed of volunteers for the practice accreditation program and therefore not nationally representative for primary care practices in the country. This reflects current practice, in which practice accreditation is a voluntary activity. It implies that study results cannot be generalized to the (currently hypothetical) situation of obligatory accreditation. Furthermore, we only collect data on CVRM; therefore, we cannot make statements about the effects of the program on other chronic illnesses.

Because both intervention and control groups start with accreditation, this project cannot pick up non-specific effects of the practice accreditation program. For example, we expect that practices prepare for accreditation by improving their practice (*e.g.*, involve a practice nurse). We intend to compare the groups with other, independent samples of practices that provide data on cardiovascular care to get an impression of the representativeness of our sample of practices.

With the results of this study, we hope to make a contribution with regard to further development and adjustment of the practice accreditation program. Previous research [32] has shown that the program is time-consuming for participating practices. Furthermore, it costs a considerable amount of money to participate in the program. It is important to gain more information about the effectiveness and efficiency of the program to assess if participation is worthwhile regarding the quality of CVRM. With these results, stakeholders can make policy and management decisions with regard to the use of the program.

No data cleaning or analysis has occurred prior to submission of the manuscript.

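### The adjustment covariates are scheduled for measurement at follow-up, but the primary model needs them as baseline differences and no baseline source is designated

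*Protocol article*

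**What the plan says.** Three sections of the protocol article bear on this.

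- **Other measures, item 2 (potential confounders).** "At follow up, potential confounders will be measured". For patients: "These include patient characteristics, particularly patient age, gender and multi-morbidity". For practices, the list is practice size, physician workload, volume of assistance, "delegation of medical tasks to assistants, and involvement of practice nurses in chronic care".
- **Process evaluation.** The telephone interview takes place "after data collection for follow-up measurement is concluded". "Topics of this interview are: practice characteristics; feedback reports; composing improvement plans" are among its subjects, so practice characteristics appear there as follow-up information too.
- **Statistical methods.** "The study groups will be compared at baseline regarding known determinants of cardiovascular care and its improvement". The patient examples are age, multi-morbidity and practice-level ethnicity. The practice examples are "availability of nurses, delegation of medical tasks to assistance, practice size". Factors on which the arms differ at baseline then enter the logistic model for each outcome. Candidates are limited to factors known from previous research, with the aim of avoiding overcorrection.

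The baseline data are described under Ethical approval and Measurement procedures as the cardiovascular indicators from the accreditation audit. The description of the accreditation program mentions a practice-management instrument (VIP), but nothing links it to the covariates.

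**The concern.** A covariate that serves as a baseline difference has to be measured before randomisation. The only measurement time given for these practice factors is follow-up, after a period in which one arm was told to work on cardiovascular care and the other on different areas. Followed literally, the plan has two consequences.

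First, the stated baseline comparison of practice characteristics cannot be made from the data described.

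Second, if follow-up values stand in for baseline values, the selection rule works against the trial. Covariates enter because the arms differ, and a difference produced by the improvement work would itself trigger the adjustment. Adjusting for a factor on the path from intervention to outcome removes the part of the effect that runs through it. The limit to factors with prior evidence does not help, because it restricts which factors are eligible and not when they are measured.

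The primary analysis is at stake. Practice data not recorded before randomisation may also be impossible to recover later.

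**Working it through.** **1. The two lists side by side**

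| Factor | Other measures (at follow-up) | Statistical methods (compared at baseline) |
|---|---|---|
| Patient age | yes | yes |
| Multi-morbidity | yes | yes |
| Gender | yes | not among the examples |
| Practice size | yes | yes |
| Task delegation | yes | yes |
| Practice nurses | involvement | availability |
| Workload, volume of assistance | yes | not among the examples |
| Ethnicity (practice level) | not listed | yes |

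The lists overlap in the factors that matter here but are not identical. Both sections cite the same source for the practice characteristics.

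**2. Which factors can change after randomisation**

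Age and gender cannot be affected, and practice size hardly. Workload, assistance, delegation and nurse involvement can change, and recorded multi-morbidity might. The Discussion confirms this in principle: "we expect that practices prepare for accreditation by improving their practice", with involving a practice nurse as its example.

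**3. The plan's own sample size**

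Inputs from the Sample size section: 55% against 65%, power 0.80, alpha 0.05 (two-sided assumed), ICC 0.05, 30 patients per practice.

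- Individually randomised: 376 patients per arm.
- Design effect: 1 + (30 − 1) × 0.05 = 2.45.
- Practices per arm: 376 × 2.45 / 30 = 30.7, so 31. This reproduces the stated figure.
- Power for 10 points: 0.804 with 31 practices per arm, 0.849 with 35.

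**4. Possible size of the bias**

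The documents give no figures for this step. The assumptions are a total effect of 10 points, a practice factor that moves 20 points more in the intervention arm than in control, and a factor worth 10 points on the outcome.

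Adjusted effect = total effect − (shift by arm × effect of factor) = 10 − 0.20 × 10 = 8 points.

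If the factor moved 20 points more in the control arm, the same formula gives 10 + 0.20 × 10 = 12 points, an inflated effect.

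Over a wider assumed range (shift 10 to 30 points, factor worth 5 to 15 points), the adjusted effect runs from 10 − 0.10 × 5 = 9.5 down to 10 − 0.30 × 15 = 5.5 points. With no shift by arm there is no change.

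**5. Dependence on the model**

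Simulation with the 20-point shift and the factor worth 10 points:

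| Analysis | Without the factor | Adjusted for its follow-up value |
|---|---|---|
| Follow-up comparison only | 10.0 | 7.9 |
| Follow-up comparison, also adjusted for baseline outcome | 10.0 | 8.9 |
| Group-by-moment contrast, factor as practice-level main effect | 10.0 | 10.0 |

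The last row has a simple reason. A factor recorded once has the same value for a practice's baseline and follow-up records. In a balanced linear model it is then orthogonal to the difference in change and cannot alter it. The figure of 8.9 depends on how closely baseline and follow-up results are related, so it is only indicative.

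For the first row, an effect of about 8 points would have power 0.611 with 31 practices per arm and 0.664 with 35.

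**The case against.** The strongest reply is that the planned model is not a follow-up-only comparison. The Statistical methods section relates each outcome to group and measurement moment, with random coefficients, and the natural effect measure in such a model is the group-by-moment contrast. A factor measured once and entered as a main effect leaves that contrast essentially untouched. This stands, and it removes any claim that the plan as written must lose 2 points. It does not settle the matter, because the section does not state the interaction or how the covariates enter, so the protection is not secured.

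Three stronger inferences are tempting and are not supported.

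- A reader might infer from the Discussion that the intervention raises nurse involvement. That remark concerns preparation for accreditation, which both arms undergo. It shows that the factor can change, not that it changes differently by arm.
- A reader might infer that follow-up values are stated to enter the model, or that no baseline values exist. Neither is said. The model is to use baseline differences, and the practice-management audit may hold some of the items. What the article lacks is any designation of that source.
- A reader might infer bias towards zero. Control practices also carry out improvement work, so the shift could favour either arm.

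It can also be argued that a condensed article leaves covariate sources to a fuller document. That would excuse silence, but here a measurement time is stated and it conflicts with the stated use.

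**Conclusion.** The point holds as a contradiction on timing within the primary analysis. The factors are scheduled for follow-up, required at baseline, and have no designated pre-randomisation source. That part rests on the text alone.

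The consequence is conditional. Bias is possible, in either direction, if follow-up values of changeable practice factors are used, if those factors shift differently by arm, and if the effect is not estimated as a group-by-moment contrast. With a 20-point shift and a factor worth 10 points, both assumed, the loss is about 2 of 10 points in a follow-up-only comparison and essentially none in the group-by-moment contrast. The sample size is not in dispute. Severity is moderate: the conflict should be resolved, but the documents do not show that the planned primary estimate is biased.

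**What to change.** - Record practice size, workload, volume of assistance, delegation and nurse involvement before randomisation. The Intervention group section already places a telephone contact and data collection ahead of randomisation. The baseline practice-management audit can serve instead if it holds these items; the protocol should then name it as the source.
- Allow only pre-randomisation practice values, plus patient age and sex, in the primary model.
- Keep follow-up values of nurse involvement and delegation for the process evaluation, where they help to explain change.
- Bring the timing in Other measures and Statistical methods into agreement.

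The cost is a few questions at enrolment, or use of existing audit data, and one sentence of wording. The sample size stays at 31 practices per arm, 35 with the dropout allowance.
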